## Abstract

**Background:**

Each year in the UK 2000 children attend emergency departments and 500 are admitted to hospital following a bath water scald. The long term effects can include disability, disfigurement or psychological harm and repeated skin grafts may be required as the child grows. The costs of treating a severe scald are estimated at 250,000 GBP. Children living in the most deprived wards are at greatest risk of thermal injuries; hospital admission rates are three times that for children living in the least deprived wards.

Domestic hot water, which is usually stored at around 60 degrees Celsius, can result in a second-degree burn after 3 seconds and a third-degree burn after 5 seconds. Educational strategies to encourage testing of tap water temperature and reduction of hot water thermostat settings have largely proved unsuccessful. Legislation in the USA mandating pre-setting hot water heater thermostats at 49 degrees Celsius was effective in reducing scald injuries, suggesting passive measures may have a greater impact. Thermostatic mixer valves (TMVs), recently developed for the domestic market, fitted across the hot and cold water supply pipes of the bath, allow delivery of water set at a fixed temperature from the hot bath tap. These valves therefore offer the potential to reduce scald injuries.

**Design/Methods:**

A pragmatic, randomised controlled trial to assess the effectiveness of TMVs in reducing bath hot tap water temperatures in the homes of families with young children in rented social housing. Two parallel arms include an intervention group and a control group where the intervention will be deferred.

The intervention will consist of fitting a TMV (set at 44 degrees Celsius) by a qualified plumber and provision of educational materials. The control arm will not receive a TMV or the educational materials for the study duration but will be offered the intervention after collection of follow-up data 12 months post randomisation.

The primary outcome measure will be the bath hot tap water temperature. Fifteen families per arm are required to detect a reduction in the mean bath hot tap water temperature from 60.4 degrees Celsius (SD 9.1) in the control group to 46 degrees Celsius in the intervention group, with 90% power and a 5% significance level (2 sided). Secondary outcome measures including acceptability will require a sample size of 120 participants.

**Discussion:**

Whilst TMVs have the potential to reduce scald injuries, to date there have been no randomised controlled trials assessing their effectiveness, acceptability and cost effectiveness.

**Trial Registration:**

ISRCTN21179067

## Background

Each year in the UK approximately 2000 children attend emergency departments and 500 are admitted to hospital following a bath water scald. Most (86%) admissions occur in children under 5 years of age and 67% of these involve a prolonged inpatient stay (5 days or more) or transfer to a specialist hospital or burns unit [1]. There has been no discernible downward trend in attendances [1] or admissions for bath water scalds over recent years [2]. The long-term effects can include disability, disfigurement or psychological harm and repeated skin grafts may be required as the child grows. The cost of treating a severe scald has been estimated at £250,000 [1]. Those at greatest risk of burn and scald injuries are those living in the most deprived wards, where the hospital admission rate is three times that for children living in the least deprived wards [3].

Bath hot tap water scalds most commonly occur amongst pre-school children, either when a child falls or climbs unsupervised into the water. More rarely a child or his/her sibling turns on the hot tap, or parents or siblings put a young child into bath water that is too hot [1,4]. Younger children are more likely to suffer more severe scalds, with a greater body surface area being involved than in scalds in older children [1,5].

Water at 60 degrees Celsius can result in a second-degree burn after 3 seconds and a third-degree burn after 5 seconds in adults [1], with even shorter exposures required to produce burns in children [6]. The Child Accident Prevention Trust therefore recommends a bath hot tap water temperature no higher than 46 degrees Celsius [7]. However, boiler and immersion heater thermostats are frequently set at 60 degrees Celsius or above [8,9]. A UK study of over 200 electric immersion heaters found 71% were set at temperatures above 65 degrees Celsius [10] and a recent survey of 165 homes in Wakefield, UK, found a mean bath hot tap water temperature of 60.4 degrees Celsius [11]. Infants' and toddlers' baths are typically in the range 32 to 41 degrees Celsius and adults' baths in the range 34 to 45 degrees Celsius [8]. Hence current tap water temperatures in many homes are high enough to cause severe burns and are much higher than the temperatures that families usually bathe at.

Scald prevention interventions aimed at encouraging families to test their hot water temperature have had only limited success. Fewer than half the families who received counselling by paediatricians and a free thermometer, tested their water temperature [12]. A mass media campaign which provided 140,000 free thermometers did not result in an increase in hot tap water temperature testing, and only half of those that tested their water and found it to be above 54 degrees Celsius lowered the water heater thermostat temperature [13]. Interventions aimed at encouraging families to reduce water heater thermostat settings in Canada and Australia have also had limited success; either because the majority did not reduce the setting [14] or reduced it insufficiently to reach the recommended safe setting [15].

Interventions not requiring active participation by families have been more successful in reducing tap water temperatures. Legislation in the USA in 1983 requiring new water heaters to be pre-set at 49 degrees Celsius was associated with a reduction in the percentage of homes with tap water temperatures above 54 degrees Celsius from 80% to 23% over the five year period post legislation [16]. Hospital admission rates, the total body area burned, the proportion requiring grafting and the proportion scarred were all lower in the period 1979 to 1988 than in the 1970s [16].

Thermostatic mixer valves do not rely on active participation by families. They restrict hot bath tap water temperatures but do not reduce the temperature of stored hot water or interfere with heating systems, and allow a supply of hotter water to different sites within the home. They are fitted across the hot and cold water supply pipes to the bath, allowing the hot bath tap water to be set at a fixed temperature, in spite of pressure and temperature fluctuations in the water supply system. A pilot project in the USA fitted 20 anti-scald devices in the homes of families with pre-school children in 1993. These devices were effective in reducing tap water temperature, but 19 of the 20 needed to be removed in the first 9 months after fitting due to sediment build up [17]. A recent small uncontrolled study in California found a lower hospital admission rate for childhood scalds in areas which received a scald-prevention program which included fitting anti-scald devices in 37 homes, but only 60% of valves remained fitted and functional 6 to 12 months after fitting [18]. An evaluation of the 'Hot Water Burns Like Fire' campaign in Queensland, which included legislation mandating fitting hot water tempering valves in new homes, those undergoing major renovation or having a new hot water system, found a significantly higher hot water temperature and scald injury rate post-legislation than pre-legislation [19]. To date there have been no randomised controlled trials assessing the effectiveness, acceptability and cost-effectiveness of thermostatic mixing valves.

Funding is provided for social housing in England by the Housing Corporation. Recent amendments to its Scheme Development Standards for housing projects receiving Social Housing Grant require TMVs to be fitted to all hot water taps in properties for older people and to bath taps in all other properties [20]. In Scotland, changes were made to the Scottish Building Standards in 2006, requiring TMVs to be fitted in homes being built or undergoing major refurbishment [21]. However, there is still no requirement for TMVs to be fitted in general housing in England and Wales, and demonstrating the effectiveness and cost-effectiveness of TMVs will be important in driving TMV policy development.

### Objectives

The objectives of this research are to:

1. assess the effectiveness and cost effectiveness of TMVs in reducing bath hot tap water temperature in the homes of families with pre-school children living in rented social housing

2. assess the acceptability of TMVs to families with pre-school children living in rented social housing

3. assess the impact on bath time safety practices (i.e. adverse and potentially adverse effects from fitting TMVs, such as use of less safe methods of obtaining hotter bath water, reduced supervision or omitting to check water temperature on the assumption that it is safe)

### Design

Pragmatic parallel arm randomised controlled trial to assess the effect of TMVs in reducing bath hot tap water temperatures in the homes of families with young children in rented social housing.

### Participants

Families with pre-school children living in Glasgow Housing Association (GHA) housing. Families will be excluded if they are not GHA tenants, if their bathroom pipe work is found to be unsuitable for fitting a TMV or if they are already participating in on-going tap water scald prevention studies.

A range of recruitment strategies will be used. These will include:

(a) written invitation from GHA to (i) GHA tenants on the East End Child Safety Project (EECSP) Database, which is a database of families who have taken part in a previous child safety project and (ii) to tenants aged 18 to 40 years identified from the GHA tenant database.

(b) face-face contact with (i) local housing organisations (LHOs) who will provide information about the study to families due to have kitchen or bathroom refurbishments or other repairs which necessitate the LHO to visit the family's home and to families at open days and other events, and (ii) local projects or organisations such as the EECSP and the Parents and Children Together (PACT) team will provide information about the study to GHA tenants they meet during project activities

(c) articles describing the study will be placed in LHO newsletters and local newspapers and GHA tenants who would like to know more about the study will be asked to contact the research team.

Families expressing interest in participating will be contacted by the research team to discuss the study, answer any questions and assess eligibility. Those agreeing to participate will be asked to complete a baseline questionnaire, which families can choose to complete by telephone or by post.

### Interventions

Participating families will be randomised to the intervention or control arm. The two arms of the trial are:

Intervention arm, where families will be offered:

• An educational leaflet devised by the research team sent to the participant prior to installation of TMV.

• A TMV valve fitted to the hot and cold bath water supply by a qualified plumber from City Building (Glasgow) Limited Liability Partnership. The maximum temperature at which this will be set will be 44 degrees Celsius (the valves have a +/- 2 degrees Celsius tolerance; hence the maximum water temperature should not exceed 46 degrees Celsius).

• An educational hanger on how to use TMV to be attached to the tap by the plumber at installation.

Control arm, where families will be offered the intervention *after *collection of follow-up data.

### Outcome measures

#### Definition of primary and secondary outcome measures

The primary outcome measure will be the bath hot tap water temperature at 3 and 12 months post installation of TMV (intervention group) or post randomisation (control group).

Secondary outcome measures will include:

a) Intervention arm only:

• TMV problems (failures, replacements, repairs or removals and reasons why TMVs are repaired, replaced or removed).

• Adjustment of temperature setting of TMVs by families.

• Satisfaction with TMVs.

• Cost of fitting TMVs and of any TMV problems.

b) Both intervention and control arms:

• A bath hot tap water temperature = 46 degrees Celsius.

• Satisfaction with bath hot tap water.

• Bath time safety practices (e.g. bath time supervision, use of other methods to increase bath water temperature, checking bath water temperature).

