#### Follow-up data collection

##### Primary outcome measure

A random sample of 15 families in each arm, who did not have their tap water temperature measured at baseline, will be chosen to have their tap water temperature measured at 3 months post fitting of TMVs and a separate random sample of 15 families in each arm will be selected to have their tap water temperature measured at 12 months post fitting of TMVs. Families will be offered a £10 voucher for use in local stores to increase response rates for water temperature measurements [22]. Measurements will be made in the same way as at baseline.

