##### Secondary outcome measures

Secondary outcomes will be measured at 12 months post installation of TMVs (intervention arm) and at 12 months post randomisation (control arm). Data will be collected by questionnaire, which families can choose to complete by telephone or by post. The follow-up questionnaire will include questions on bath time safety practices, bath time supervision and satisfaction with hot water supply. Intervention arm families will also be asked questions about satisfaction with the TMV and the fitting process, attempts to adjust the TMV temperature setting, TMV problems, occupational details and work time lost as a result of TMV fitting or problems. TMV problems will also be ascertained from repair requests or complaints made to GHA by families. Families who complete the follow-up questionnaire will be offered a £5 gift voucher for use in local stores to increase response rates [22].

The design of the follow-up questionnaire will be informed by interviews with a sample of approximately 15 families in rented social housing who have had TMV valves fitted. A purposive sample of families will be obtained, as described above, but also, if possible, to include families with differing sites of installation of TMVs, and those who have experienced TMV failures. Interviews will be used to explore families' attitudes towards TMVs, experiences of using TMVs, attempts at altering temperature settings on TMVs and any changes in safety behaviour or bath time supervision following the fitting of TMVs. They will also be used to inform the development of questions on satisfaction with TMVs, bath time safety and supervision.

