### Randomisation

After giving informed consent, families will be randomised to treatment arms. The randomisation schedule will be generated by the trial statistician using a computerised random-number generator in Stata [23], using a permuted block design with a random block size. Equal numbers will be allocated to the two groups. No stratification will be used. Group allocations will be placed in sequentially numbered, opaque, sealed envelopes. These will be opened sequentially by a researcher independent of the research team after participants have consented. The independent researcher will inform the study research fellow of the allocation who will inform GHA of the allocation. The research fellow will write to each family informing them of the allocation and provide details of how they will be contacted by GHA to organise water temperature measurement and TMV fitting.

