### Analysis

The analysis will conform to a pre-specified analysis plan. Bath hot tap water temperatures will be described using the mean and standard deviation, or median and interquartile range, depending on the distribution of temperatures. The primary analysis will compare temperatures between treatment arms using an unpaired t-test to estimate the difference between the means and its 95% CI, assuming assumptions for undertaking these analyses are met. If assumptions are not met and no suitable transformation can be found, temperatures will be compared between treatment arms using the Mann-Whitney U test.

An intention to treat analysis will be undertaken replacing missing 3 and 12 month water temperatures (excluded participants and those where access could not be gained to homes for temperature measurement), with baseline temperatures, or where baseline temperatures are unavailable they will be replaced by the mean or median temperature for that treatment arm, dependent on the distribution of the temperatures.

The proportion of families with a bath hot water temperature ≤ 46 degrees Celsius will be compared between treatment arms using χ^2 ^tests and logistic regression to estimate the odds ratio and its 95% CI. Outcomes measured on an ordinal scale will be compared between treatment arms using χ^2 ^tests for trend, or will be dichotomised and analysed as binary variables depending on the distribution of responses.

Sensitivity analyses will be undertaken to examine the effect of adjusting for baseline temperature. Where baseline temperatures are unavailable they will be replaced by the mean or median temperature for that treatment arm, dependent on the distribution of the temperatures. These analyses will be undertaken using linear regression or a Mann-Whitney U test based on change scores.

The proportion of families in the intervention arm who have TMVs removed, replaced or repaired and who adjust the temperature setting of the TMV will be described using proportions and 95% CI.

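### Follow-up is timed from valve installation in one arm and from randomisation in the other, so a never-fitted intervention family has no measurement date and the missing-data rule can give it a valve-level temperature

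*Protocol article*

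**What the plan says.** **Time origin.** The section Definition of primary and secondary outcome measures places the primary outcome "at 3 and 12 months post installation of TMV (intervention group) or post randomisation (control group". The Sample size section repeats this split. The section Secondary outcome measures applies it to the questionnaire: "Secondary outcomes will be measured at 12 months post installation of TMVs (intervention arm) and at 12 months post randomisation (control arm". The section on follow-up collection of the primary outcome differs. It describes families in each arm as "chosen to have their tap water temperature measured at 3 months post fitting of TMVs", although the Interventions section offers control families a valve only once follow-up data are in.

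**Pipework.** The Participants section excludes families "if their bathroom pipe work is found to be unsuitable for fitting a TMV", without saying when or in which arm this is found. Before randomisation it describes only contact from the research team: "Families expressing interest in participating will be contacted by the research team to discuss the study, answer any questions and assess eligibility". The Randomisation section then says "After giving informed consent, families will be randomised to treatment arms", and the letter that tells families their allocation is to "provide details of how they will be contacted by GHA to organise water temperature measurement and TMV fitting".

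**Missing readings.** The Analysis section announces an intention-to-treat analysis. It replaces missing 3- and 12-month temperatures, described as those of "excluded participants and those where access could not be gained to homes for temperature measurement", with the baseline temperature. Where there is none, the mean or median of the family's own arm is used. The 3-month sample is drawn from families with no baseline reading.

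**The concern.** Non-receipt is foreseeable. Valves are offered, and the Discussion expects difficulty in getting into homes to fit them. A control family with the same pipework or the same reluctance has a date at which it is due to be measured. The intervention family that is never fitted does not. If such families go unmeasured and are filled in from fitted homes, the comparison no longer estimates the effect of allocation, which is what intention to treat and the trial's pragmatic aim call for.

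Fitting delay also lengthens time since randomisation in the intervention arm only. Families who move before follow-up are withdrawn (Withdrawals section), so that arm has longer in which to lose families.

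**Working it through.** **1. The plan's own figure.** Inputs from the Sample size section: means 60.4 and 46, so a difference of 14.4 °C; SD 9.1; 90% power; 5% two-sided.
- Normal approximation: n = 2 × (1.960 + 1.282)² × 9.1² / 14.4² = 8.4, so 9 per arm.
- Noncentral t: power is 88.3% at 9 and 91.7% at 10, so 10 per arm.
- Loss of 33%: 10 / (1 − 0.33) = 14.9, so 15.

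Both stated figures reproduce. The 46 °C target equals the highest temperature expected with a valve in place (44 + 2, Interventions section), so the calculation makes no allowance for unfitted homes.

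**2. What the imputation does to the estimate.** Suppose m intervention homes are measured, all fitted, with mean M, and k unfitted homes have no baseline reading. Each of the k receives M. The arm mean is (mM + kM)/(m + k) = M, exactly as if the k homes had been deleted. The expected difference stays at 14.4 °C whatever k is.

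**3. The difference as randomised.** Let u be the share unfitted. The documents give no value, so the range is assumed. Let unfitted homes stay at the control mean of 60.4 °C (also assumed). The difference is then (1 − u) × 14.4 and the overstatement u × 14.4.

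| u | As randomised (°C) | Overstatement (°C) |
|---|---|---|
| 10% | 13.0 | 1.4 |
| 20% | 11.5 | 2.9 |
| 30% | 10.1 | 4.3 |

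With valve homes at 44 °C the difference among fitted homes is 60.4 − 44 = 16.4, and the overstatement is 1.6 °C per 10% unfitted.

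**4. What the imputation does to precision.** Take the plan's own loss: 10 of 15 measured per arm, 5 filled with the arm mean.
- Correct standard error: 9.1 × √(2/10) = 4.07.
- After imputation the SD shrinks to 9.1 × √(9/14) = 7.30, and the standard error is computed as 7.30 × √(2/15) = 2.66, a ratio of 0.65.
- In 200,000 simulated trials with no true difference, the t-test rejected in 19.6%, against 5.0% using the measured values alone.

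**5. Power if every selected family is measured.** Unfitted homes are drawn from the control distribution; 40,000 simulated t-tests per case.

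| u | Power, 10 measured per arm | Power, 15 measured per arm | n per arm for 90% (normal approximation) |
|---|---|---|---|
| 0% | 92% | 99% | 9 |
| 10% | 81% | 94% | 12 |
| 20% | 68% | 86% | 16 |
| 30% | 55% | 74% | 22 |

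**The case against.** The strongest reply is that the plan already provides for these families. A reader might infer that unfitted intervention families drop out of the comparison. The Analysis section does not say that: it names intention to treat and keeps excluded and no-access families by imputation. That stands. What it does not rescue is the estimate wherever the imputed value is the arm mean or median.

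The imputation also does not always hide non-receipt. The first substitute is the baseline temperature, a pre-valve value that would dilute the effect as it should. The 3-month sample has no baseline readings. The wording leaves open whether the 12-month sample has any, so the problem is certain to apply only to the former.

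A reader might also infer that unsuitable pipework is found and excluded after randomisation in the intervention arm only. The documents do not state this. The Participants section gives no time and no arm, and plumbers visit the first half of both arms at recruitment to take temperatures. The inference is plausible: visits for fitting are arranged after allocation, excluded participants appear among those missing follow-up readings, and no pipework inspection of control homes is described. But it remains an inference.

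Nor does the text say that a family declining a valve goes unmeasured. Samples are of families in each arm, not of fitted families. The gap is that no date is defined for such a family.

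Finally, timing from installation has a purpose, since it gives every fitted home the same valve exposure. Nothing in the documents suggests that control temperatures drift during a fitting delay. The full protocol or the analysis plan may say more, but the outcome definition and the imputation rule are stated here.

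**Conclusion.** The point holds in this form: the time origin differs by arm, a never-fitted intervention family has no defined outcome date, the timing of the pipework exclusion is not fixed, and the imputation rule can turn an intention-to-treat estimate into the effect among fitted homes.

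The figures of 1.4 °C per 10% unfitted (46 °C) and 1.6 °C (44 °C) are upper bounds. They assume that all unfitted homes are unmeasured, lack a baseline reading and would stay at 60.4 °C. Any unfitted home that is measured, or filled from its baseline, reduces the bias. Within the range shown the difference keeps its direction; its size and its confidence interval are what suffer. The loss of precision needs no assumption about fitting, only that about a third of readings are missing, as the plan itself allows.

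The documents do not support the stronger conclusions that unfitted families are discarded or that exclusion is confined to one arm.

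**What to change.** - Time both arms from randomisation, or measure each intervention family and a concurrently randomised control family on the same dates. Use the same anchor for the 12-month questionnaire.
- Measure every selected family whether or not a valve is fitted.
- Reconcile the follow-up section, which writes of fitting for both arms, with the outcome definition and the Sample size section.
- Apply the pipework criterion before randomisation, or keep unsuitable homes in their arm as not fitted.
- Do not fill missing readings with the arm mean or median.
- Report fitted homes only as a secondary analysis.
- Restate power under an assumed non-receipt rate.

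**Cost.** The first six changes are wording and scheduling. Late-fitted homes will have somewhat less valve exposure at each reading. The real cost is power: with 10 measured per arm it is about 81% at 10% non-receipt and 68% at 20%; with 15 it is about 94% and 86%. The 33% loss allowance may already include unfitted homes, so the number measured could lie between 10 and 15.

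If more readings are needed, the pool matters. With 120 recruited there are 60 per arm, of whom 30 have no baseline reading. Two samples of 15 use all 30 if both come from that group, so larger samples would have to include families with a baseline reading.
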